## Abstract

**ABSTRACT:**

**Introduction:**

Cognitive behavioural therapy (CBT) serves as a first-line treatment for internalising disorders (ID), encompassing depressive, anxiety or obsessive-compulsive disorders. Nonetheless, a substantial proportion of patients do not experience sufficient symptom relief. Recent advances in wearable technology and smartphone integration enable new, ecologically valid approaches to capture dynamic processes in real time. By combining ecological momentary assessment (EMA) with passive sensing of behavioural and physiological information, this project seeks to track daily fluctuations in symptom-associated constructs like affect, emotion regulation (ER) and physical activity. Our central goal is to determine whether dynamic, multimodal markers derived from EMA and passive sensing can predict treatment non-response and illuminate key factors that drive or hinder therapeutic change.

**Methods and analysis:**

PREACT-digital is a subproject of the Research Unit FOR 5187 (PREACT), a large multicentre observational study in four outpatient clinics. PREACT channels state-of-the-art machine learning techniques identify predictors of non-response to CBT in ID. The study is currently running and will end in June 2026. Patients seeking CBT at one of four participating outpatient clinics are invited to join PREACT-digital. They can take part in (1) a short version with a 14-day EMA and passive sensing phase prior to therapy, or (2) a long version in which the short version’s assessments are extended throughout the therapy. It is estimated that 468 patients take part in PREACT-digital, of which 350 opt for the long version of the study. Participants are provided with a smartwatch and a customised study app. We collect passive data on heart rate, physical activity, sleep and location patterns. EMA assessments cover affect, ER strategies, context and therapeutic agency. Primary outcomes on (non)-response are assessed after 20 therapy sessions and therapy end. We employ predictive and exploratory analyses. Predictive analyses focus on classification of non-response using basic algorithms (ie, logistic regression and gradient boosting) for straightforward interpretability and advanced methods (LSTM, DSEM) to capture complex temporal and hierarchical patterns. Exploratory analyses investigate mechanistic links, examine the interplay of variables over time and analyse change trajectories. Study findings will inform more personalised and ecologically valid approaches to CBT for ID.

**Ethics and dissemination:**

The study has received ethical approval from the Institutional Ethics Committee of the Department of Psychology at Humboldt Universität zu Berlin (Approval No. 2021–01) and the Ethics Committee of Charité-Universitätsmedizin Berlin (Approval No. EA1/186/22). Written informed consent will be obtained from all participants prior to enrolment. Results will be disseminated through peer-reviewed journals and presentations at national and international conferences.

**Trial registration number:**

DRKS00030915; OSF PREACT: http://osf.io/bcgax; OSF PREACT-digital: https://osf.io/253nb.

Strengths and limitations of this studyLarge sample of clinical patients starting cognitive behavioural therapy, which is rare in digital phenotyping studies.Longitudinal assessment combining passive sensing and ecological momentary assessment, capturing a dynamic, multidimensional view of participants’ behaviours, emotions and physiological states, and enabling analysis of within-person trajectories.State-of-the-art, consumer-grade wearables (Withings Scanwatch) for all participants, ensuring high-quality, standardised data collection across participants and ensuring the privacy of participants by not disclosing them as study participants.There is no healthy control group, which limits the ability to distinguish clinical from non-clinical patterns in digital phenotyping data.Participant burden due to extensive assessments might decrease adherence and influence therapy outcomes.

## Introduction

 The following study protocol describes a subproject from the Research Unit FOR 5187 ‘Towards Precision Psychotherapy for Non-Respondent Patients: From Signatures to Predictions to Clinical Utility (PREACT)’ that was formed as a collaboration across four universities and outpatient clinics in Berlin to identify predictors of non-response to cognitive behavioural therapy (CBT) in Internalising Disorders (ID). The diagnostic and experimental focus of PREACT lies on emotion regulation (ER) as a putative key mechanism of CBT and response to CBT.

Due to the comprehensive design of the Research Unit, the general study protocol provides an overview across all subprojects.^1^ The present protocol entails a more granular description of methods and objectives relevant to this subproject. This level of detail is of utter importance to ensure that reporting recommendations are met^2^ and researchers can assess the comparability with other digital phenotyping studies. Associated materials and descriptions can be found in our Open Science Framework (OSF) directory (https://osf.io/253nb) and on Github (https://github.com/[name]/preact_digital).

ID encompass a broad range of psychopathology, including symptoms of depressive disorder, obsessive-compulsive disorder or generalised anxiety disorder.^3^ They represent the most common mental health conditions worldwide.^4^ CBT is considered the first-line treatment for ID but was shown to produce insufficient response rates.^5^ In addition, urgently needed breakthroughs in psychotherapy research remain elusive: studies adapting or enhancing CBT or comparing it to other forms of psychotherapy for ID, like behavioural activation therapy or interpersonal therapy, often do not find significant differences in outcomes.^6^

A great hope lies within the field of machine learning, which has found its way into psychotherapy research within recent years.^7^ Here, a prominent approach is to predict outcomes before the treatment started using a large number of different variables from various sources.^8 9^ The idea is to change or adapt a treatment if the risk of non-response is high and thus avoid frustrating experiences for patients as well as unnecessary societal and economical burdens. Thus far, however, results are unsatisfactory: depending on the features of input, predictive accuracies often only slightly exceed chance level, like 62% for neuroimaging markers^10^ and/or fail to generalise to external samples.^11^

Most existing prediction studies relied on cross-sectional data (ie, pre-treatment self-reports). However, these momentary snapshots are incapable of depicting the intraindividual symptom heterogeneity therein.^12 13^ Beyond that, the applicability to outpatient care—as an ultimate goal of precision psychotherapy—is neglected when relying solely on time and cost-intensive forms of phenotyping like clinical interviews or neurophysiological markers.^14^

Luckily, recent advances in wearable devices and smartphone technology and the broad integration of smartphones into people’s everyday life are paving the way for more accessible, ecologically valid data collection methods. In particular, these tools offer a scalable alternative that can reduce reliance on labour-intensive procedures. Ecological momentary assessment (EMA) involves short, repeated self-reports on the smartphone. Passive sensing refers to the continuous collection of biobehavioural data (ie, physical activity and heart rate) using smartphone or wearable sensors. The combination of active (ie, EMA-based) and passive (ie, wearable-based) assessments is also referred to as ‘Digital phenotyping’.^15^ Digital phenotyping offers the opportunity to better understand individual factors and mechanisms leading to (non-) response by (a) opening the black box of between-session processes and gathering naturalistic information from everyday settings, (b) getting long-term subjective and objective impressions of symptom dynamics in (c) real time and without recall biases inherent to cross-sectional assessments.

First, systematic reviews on digital phenotyping in different ID concluded that, although in its infancy, it can identify behavioural patterns associated with ID.^16 17^ These include, for example, increased time at home in depression^18 19^ or a positive association between heart rate variability (HRV) and anxiety.^20^ At the same time, only a few studies have applied digital phenotyping (DP) in patients undergoing psychotherapy for ID to depict (absent) changes in symptoms and/or predict treatment response. De Angel *et al*^21^ collected DP data from 66 patients starting psychological treatment for depression. They only published results on the feasibility of data collection, showing that data availability varied strongly depending on data source (ie, smartphone vs wearable) and treatment stage (ie, pretreatment vs in-treatment vs posttreatment). Müller-Bardoff *et al*^22^ conducted a randomised-controlled trial (RCT) to find sensor-based and EMA-based predictors of response to CBT in 150 patients suffering from anxiety disorders. To date, they did not publish results related to DP-based outcome prediction. In psychiatric settings, Zou *et al*^23^ collected passive sensor data (ie, phone usage, app usage and sleep) from 245 patients with major depressive disorder to predict response to psychopharmacological outpatient treatment. They were able to achieve sufficient predictive accuracy around 10 weeks before treatment ended.

In summary, there remains a need for studies investigating digital phenotyping as both predictors and markers of treatment response in ID. Our subproject, PREACT-digital, addresses this gap. We implement EMA and passive sensing via state-of-the-art wearable devices to continuously monitor patients receiving CBT for ID in their daily lives. Building on the PREACT consortium’s overarching focus on ER, we incorporate ER-related constructs such as affect and social/situational context into our EMA measures. Ultimately, our goal is to identify ecologically valid, readily implementable markers of treatment response—or the absence thereof—in CBT for ID.

Our research objectives encompass predictive and exploratory hypotheses. First, in-line with PREACT, we aim to find out if we can predict non-response (NR) at T20 (ie, after 20 therapy sessions) and TPost (ie, after therapy end or 365 days if therapy lasts longer) with sufficient predictive accuracy (i.e. >75%) using a combination of EMA and passive sensing features collected during the first, 14-day assessment phase (T0). We expect that EMA-based features can better capture ER-related dynamics and are thus of greatest importance, but passive features will provide significant incremental value. We further hypothesise that EMA and sensing features both have an incremental predictive value beyond more elaborate (neuro)physiological markers and thus represent an ecologically valid substitute for implementation. Second, we aim to find out if symptom changes during CBT can be modelled using EMA and passive sensing, and how they relate to cross-sectional self-report and physiological information. We hypothesise that data actively and passively generated by personal electronic devices such as smartphones and wearables can be linked to neuroimaging-based markers of ER assessed in other subprojects of the research group.

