### Sample size calculation

As described in the main study protocol,^1^ the required sample size for the PREACT study was estimated (a) using simulation studies with fivefold cross-validation to yield a prediction accuracy of 75–80% and (b) using effect size calculation for group-based linear multiple regression analyses, resulting in a required sample of 585 patients. Of those, it was expected that around 80% would take part in PREACT-digital, resulting in an estimated sample size of 468 patients for T0. Based on previous studies investigating the feasibility of digital phenotyping in clinical samples,^28^ it was further expected that 75% of the sample would decide for the long version of the study, resulting in 350 patients providing data at T20 and TPost.

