### Outcomes

We use different machine learning techniques to predict treatment response based on DP data. To evaluate treatment response, we implement two different criteria. First, we follow the definition of the PREACT research group to achieve comparability with other subprojects. It follows the concept of clinically significant change as introduced by Jacobson & Truax.^29^ The shift from a dysfunctional to a functional mental condition is operationalised by achieving a Brief Symptom Inventory-General Severity Index (BSI–GSI) score of less than 0.56 at T20/posttreatment assessment. Additionally, the change observed from baseline to T20/posttreatment must be reliable, as defined by the Reliable Change Index (RCI). The BSI–GSI is a self-report measure assessed cross-sectionally at T20 and TPost as part of PREACT.

Second, we will use aggregates of EMA assessments on positive and negative affect (PANAS-X; 21) collected during measurement bursts at T20 and TPost as additional indicators of treatment response as EMA-based measures were shown to capture different aspects of symptom load (28).

To account for the complexity of ID, PREACT further included disorder-specific measures as secondary outcomes: The Hamilton Anxiety Rating Scale (HAM-A; 29), the Montgomery–Åsberg Depression Rating Scale (MADRS; 30), the Yale-Brown Obsessive Compulsive Scale (Y-BOCS; 31, 32) and the Clinician-Administered PTSD Scale for DSM-5 (CAPS-5; 33, 34).

Finally, for exploratory analyses, outcomes will depend on the respective research question, that is, single-beep scores of EMA constructs or cross-sectional self-reports of ER capacities.

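### The 75% accuracy criterion for predicting non-response is tied neither to the non-response rate nor to the sampling error of a hold-out of about 94 patients

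*Protocol article*

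**What the plan says.** The objectives at the end of the Introduction set the criterion. Using EMA and passive-sensing features from the first 14-day phase (T0), the study asks whether non-response at T20 and TPost can be predicted "with sufficient predictive accuracy (i.e. >75" per cent). Accuracy is also the planning target in Sample size calculation: the parent study's size was found "using simulation studies with fivefold cross-validation to yield a prediction accuracy of 75–80" per cent, together with a regression-based calculation.

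Under Outcomes, response needs two things together: a BSI-GSI "score of less than 0.56 at T20/posttreatment assessment", and a change from baseline that "must be reliable, as defined by the Reliable Change Index (RCI"). Everyone else is a non-responder. Sample selection admits only patients with a BSI-GSI above 0.56.

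The section on data freeze and hold-out sets aside 20% of the cohort, stratified by age, sex, primary diagnosis and data modality. Model development evaluates the final pipeline on that hold-out.

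Predictive analyses adds two relevant plans:
- Accuracies are to be compared between measurement bursts and between T20 and TPost.
- Sets of models are to be compared by paired AUC differences with 95% CIs and DeLong tests, against a cross-sectional baseline model.

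The article states no expected non-response rate, no no-information rate, no balanced accuracy and no confidence-bound rule for the 75% threshold.

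**The concern.** A given accuracy means something only against what can be had without any predictor. That level is the share of the larger outcome class (the no-information rate), and it equals 50% only when the classes are balanced. The article itself judges earlier work this way, noting that "predictive accuracies often only slightly exceed chance level, like 62% for neuroimaging markers", but it sets its own threshold without such a reference.

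Balance cannot be presumed here. All patients enter above the cut-off, and one who crosses it without reliable change still counts as a non-responder. The hold-out is not stratified by outcome either, so its class shares may differ by chance from those of the development set.

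Two things are at stake:
- The statement that non-response is predicted with sufficient accuracy could reflect case mix rather than skill, or could rest on an estimate too imprecise to carry it.
- If the non-response rate differs between T20 and TPost, accuracy can move between them with no change in discrimination. The accuracy of a rule that labels everyone a non-responder simply equals the non-response rate at each timepoint.

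**Working it through.** **Inputs from the article.** Parent sample: "resulting in a required sample of 585 patients". Uptake: "around 80% would take part in PREACT-digital, resulting in an estimated sample size of 468 patients for T0". Long version: "75% of the sample would decide for the long version of the study, resulting in 350 patients providing data at T20 and TPost". Hold-out fraction 20%; threshold above 75%; planned accuracy 75–80%.

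**Assumed input.** The share of the larger outcome class is not given, so it is varied from 60% to 80%.

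**1. The plan's own figures.** 585 × 0.80 = 468, as stated. 468 × 0.75 = 351 against 350 stated, which is rounding. The 585 comes from simulations in the main protocol whose inputs are not given here, so it cannot be re-derived.

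**2. Size of the hold-out.** 0.20 × 468 = 93.6, about 94. This is an upper figure, before missing outcomes and compliance exclusions.

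**3. Smallest result above 75%.** 0.75 × 94 = 70.5, so at least 71 correct (71/94 = 75.5%).

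**4. A rule without predictors.** If every patient is given the majority label and that class has share π, the number correct is X ~ Binomial(94, π). The chance of exceeding 75% is P(X ≥ 71):

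| Assumed majority share π | P(X ≥ 71) |
|---|---|
| 60% | 0.1% |
| 65% | 1.9% |
| 70% | 14% |
| 75% | 51% |
| 80% | 89% |

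The effect is negligible at 60–65% and serious from about 70%.

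**5. Precision at the threshold.** The normal-approximation half-width is 1.96 × √(0.75 × 0.25 / 94) = 0.0875, or ±8.8 points. The exact (Clopper-Pearson) 95% CI at 71/94 is 65.6% to 83.8%.

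**6. What it takes to show accuracy above 75%.** The smallest count whose exact 95% lower limit exceeds 75% is 79/94 (84.0%). The chance of reaching it is:
- P(X ≥ 79 | 94, 0.80) = 0.199, about 20%, at the top of the planned range;
- P(X ≥ 79 | 94, 0.85) = 0.667, about 67%, above that range.

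For scale, 80% power to show more than 75% when the truth is 80% (two-sided 5%, normal approximation) needs n = [(1.960 × √(0.75 × 0.25) + 0.842 × √(0.80 × 0.20)) / 0.05]², about 563 test patients.

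**7. Precision of balanced accuracy.** Assume sensitivity and specificity of 75% and non-response of 70%. The 94 patients then split into about 66 and 28, and the half-width is 1.96 × ½ × √(0.1875/66 + 0.1875/28) = 0.096, or ±9.6 points. This is wider than the ±8.8 points for accuracy.

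**The case against.** The strongest reply has five parts.

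- **The metric may be defined elsewhere.** The article says only predictive accuracy, aligns the aim with PREACT, and refers to a main protocol that is not shown. That document may give the assumed non-response rate or a weighted metric. This stands as a caveat, but the article describes itself as the more granular account and states the bare threshold.
- **The non-response rate is unknown.** A reader might infer from the strict response definition that non-response is the large majority, so that a useless model would pass. The article gives no figure to support this, and at 60–65% such a rule almost never passes. The point is therefore conditional.
- **AUC is already planned.** A rule that labels everyone alike has an AUC of 0.5, so the planned comparisons would expose it. This is correct and lowers the risk of a misleading report. But those comparisons rank model sets; they carry no success threshold and do not qualify the 75% criterion.
- **The hold-out is not the only evidence, and no test against 75% is planned.** A reader might infer that the criterion cannot be verified at all. That goes too far: at a true accuracy of 85% the hold-out would show it two times in three, and repeated cross-validation on about 374 development patients (468 − 94) gives a second estimate. Still, the hold-out is the stated final evaluation.
- **The timepoint comparison is exploratory.** True, and it is distorted only if non-response rates differ.

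It is also tempting to apply the smaller long-version hold-out (0.20 × 350 = 70). It does not fit this criterion: T0 features come from both versions, and the BSI-GSI is collected in the parent study. It matters only for models that use later bursts.

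**Conclusion.** The point holds in conditional form. As written, the criterion would accept any model above 75% on the hold-out, whatever the majority share and however wide the interval.

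How much the missing base rate matters depends on a figure that the article does not give. A predictor-free rule passes about 2% of the time or less at a majority share up to 65%, 14% at 70%, and half the time or more from 75%.

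The imprecision does not depend on that figure. A result just above the threshold is compatible with true accuracy from about 66% to 84%. Within the planned 75–80% range, the chance of a lower limit above 75% is at most about 20%.

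These results assume 94 evaluable hold-out patients, independent predictions and plain accuracy as the metric. Losses would widen the intervals. The documents do not show that the criterion will be met by an uninformative model, or that it can never be verified. They show that it does not guard against the first and says nothing about the uncertainty.

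**What to change.** 1. State the expected non-response rate at T20 and at TPost.
2. Keep the 75% accuracy target for comparability with PREACT, but call prediction sufficient only if one further condition, chosen in advance, is met: either the 95% lower limit of hold-out accuracy lies above the observed no-information rate, or the 95% lower limit of the AUC lies above 0.5. Both serve the same purpose, and the AUC will already be computed for the planned comparisons.
3. Report hold-out accuracy with its 95% CI beside the no-information rate, and balanced accuracy with its own, wider CI (about ±9.6 points under the assumptions in the working).
4. Compare bursts, and T20 with TPost, by AUC or balanced accuracy instead of accuracy.

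The cost is a few sentences and no new data. The criterion becomes somewhat harder to meet: at 71/94, the accuracy condition holds only if the no-information rate is below 65.6%. The change does not make the hold-out large enough to establish accuracy above 75% within the planned range; the reported interval makes that limit visible.

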## Method and analysis

### Sample selection

Participants within the PREACT study are informed about PREACT-digital via flyers and information brochures within each of the participating outpatient clinics. Interested patients are invited to an ‘onboarding’ meeting to review inclusion and exclusion criteria and provide written informed consent. The inclusion criteria of the PREACT study are as follows: (1) age of 18 years or older, (2) a primary diagnosis based on the DSM-5 criteria for either social anxiety disorder, panic disorder, agoraphobia, generalised anxiety disorder, obsessive-compulsive disorder, posttraumatic stress disorder or unipolar depressive disorder (major depression or dysthymia), (3) an indication for outpatient CBT treatment, (4) a minimum treatment plan of 12 sessions, (5) a symptom severity indicated by a General Severity Index of the Brief Symptom Inventory (BSI-GSI) greater than 0.56 (19, 20), (6) a Clinical Global Impression – Severity Scale (GSI-S) score of 3 or higher, indicating at least mild illness, and (7) owning an appropriate smartphone (ie, android version >9.0 or i-Phone version >15.0).

Exclusion criteria encompass contraindications for outpatient treatment, including: (1) a current secondary diagnosis of moderate to severe substance use disorder (including regular use of benzodiazepines), (2) current psychosis, (3) current bipolar disorder, (4) more than moderate suicidality, (5) medical conditions that contraindicate CBT according to the medical consultation report (ie, severe cognitive impairment or dementia). Patients who require inpatient treatment during the course of the outpatient treatment will be excluded.

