### Study procedures

The PREACT-digital study is currently running and will end in June 2026. Interested patients can choose if they want to take part in PREACT-digital (ie, therapy-accompanying digital phenotyping). Individuals who decide to participate in the PREACT-digital can choose between two study versions. Option 1 (‘the short version‘) consists of a 14-day EMA assessment phase paralleled by passive data collection prior to therapy start (T0) only. Option 2 (‘the long version’) consists of one additional EMA phase after 20 therapy sessions (T20) and one after the end of therapy (if the duration of therapy exceeds 1 year, data are collected 365 days after therapy start; TPost). Passive data are collected in parallel throughout the entire time. Participants enrolled in the short version have the option to switch to the long version after they have completed the first assessment phase. The design of our subproject is depicted in figure 1.

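### Excluding patients who come to need inpatient treatment during CBT selects the prediction cohort on a later event that is unknown at T0 and plausibly related to non-response

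*Protocol article*

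**What the plan says.** The Sample selection section first lists numbered exclusion criteria that describe a patient's state at entry: current diagnoses, suicidality, and medical conditions that speak against CBT. It then adds a rule of a different kind: "Patients who require inpatient treatment during the course of the outpatient treatment will be excluded".

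The Introduction sets the predictive objective: "we aim to find out if we can predict non-response (NR) at T20 (ie, after 20 therapy sessions) and TPost". The predictors are EMA and passive-sensing features from the first assessment phase, and the accuracy aimed for is above 75%. Study procedures places that phase before treatment; the short version consists of "a 14-day EMA assessment phase paralleled by passive data collection prior to therapy start (T0) only".

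Under Outcomes, response requires "achieving a Brief Symptom Inventory-General Severity Index (BSI–GSI) score of less than 0.56 at T20/posttreatment assessment" together with a change from baseline that is reliable by the Reliable Change Index. Admission to hospital is not part of this definition.

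The section on data freeze and hold-out draws a 20% hold-out at participant level from the cohort and leaves 80% for development. None of the outcome, preprocessing, model-development or predictive-analysis sections says how a patient with an inpatient stay is classified or whether that patient's T0 data are kept. The limitations in the Discussion are the missing control group and participant burden; this selection is not among them.

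**The concern.** A prediction model should be developed and tested on the patients to whom it will be applied, defined by what is known when it is applied. Here that moment is T0. Nobody knows at T0 who will later need inpatient treatment, so a cohort from which those patients have been removed is defined by future information.

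The removal is also unlikely to be neutral. A patient who comes to need inpatient care during outpatient CBT is plausibly less likely than others to reach the BSI-GSI threshold with reliable change. If so, the rule takes non-responders out of a study whose purpose is to recognise them early. The Discussion names intensified care as a possible use of the predictions, and the removed patients are close to that use.

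The hold-out gives no protection. It is drawn from the same cohort as the development data, so a rule applied to the cohort acts on both parts, and good hold-out performance would not reveal the selection.

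**Working it through.** **The plan's own figures.** From Sample size calculation: 585 × 0.80 = 468 at T0, as stated. 468 × 0.75 = 351 for the long version, against 350 stated, which is rounding. The 585 itself rests on simulations in the main protocol, which is not shown. None of these figures is in dispute. They only set the scale.

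**Inputs that the documents do not give.** These are assumptions, shown as ranges:
- h, the share of patients excluded for inpatient treatment: 2%, 5%, 10%. Of 468 patients this is about 9, 23 and 47.
- p, the true non-response rate: 40%, 50%, 60%.
- All excluded patients are non-responders. This is the extreme case and is relaxed below.

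**Formulas.** Observed non-response rate after exclusion = (p − h)/(1 − h). Share of all non-responders lost = h/p.

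| p | h | Observed rate | Fall (points) | Non-responders lost |
|---|---|---|---|---|
| 40% | 2% | 0.38/0.98 = 38.8% | 1.2 | 5.0% |
| 40% | 5% | 0.35/0.95 = 36.8% | 3.2 | 12.5% |
| 40% | 10% | 0.30/0.90 = 33.3% | 6.7 | 25.0% |
| 50% | 2% | 0.48/0.98 = 49.0% | 1.0 | 4.0% |
| 50% | 5% | 0.45/0.95 = 47.4% | 2.6 | 10.0% |
| 50% | 10% | 0.40/0.90 = 44.4% | 5.6 | 20.0% |
| 60% | 2% | 0.58/0.98 = 59.2% | 0.8 | 3.3% |
| 60% | 5% | 0.55/0.95 = 57.9% | 2.1 | 8.3% |
| 60% | 10% | 0.50/0.90 = 55.6% | 4.4 | 16.7% |

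Over the grid, 3.3% to 25% of non-responders are lost, and the observed rate falls by about 1 to 7 points.

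**If only a share q of the excluded are non-responders.** The observed rate becomes (p − qh)/(1 − h), and the share lost becomes qh/p. The rate falls only if q exceeds p, that is, only if non-response is more common among the excluded than in the whole cohort. That is plausible, but the documents do not establish it.

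**Effect on accuracy.** Take p = 50% and h = 10%, and let the model have 75% sensitivity and 75% specificity in the retained patients. Let it detect a share s of the excluded non-responders. With these patients put back:
- accuracy = 0.40 × 0.75 + 0.10 × s + 0.50 × 0.75 = 0.675 + 0.10s
- sensitivity = (0.40 × 0.75 + 0.10 × s)/0.50 = 0.60 + 0.20s

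At s = 0.50, accuracy is 72.5% and sensitivity 70%. At s = 0.75, both are 75%. At s = 0.95, accuracy is 77.0% and sensitivity 79%. The restricted cohort can therefore flatter the model or understate it, depending on whether the admitted patients are harder or easier to recognise at T0.

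**The case against.** Five objections deserve an answer.

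*The word for exclusion is ambiguous.* It may mean only that study assessments stop, and no analysis section says that T0 data are deleted. This stands as far as it goes, so the action of the rule on both data sets is what follows if it is applied as written; the article does not report it as done. The problem remains under the narrower reading. If assessments stop, the T20 or TPost BSI-GSI is missing for a reason plausibly tied to the outcome. The article's missing-at-random statement concerns skipped measurements in the dynamic structural equation models and does not cover this.

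*The main protocol or the posted analysis code may settle it.* Possibly, and the lack of a detailed handling rule in an article is not the complaint. The complaint is the exclusion sentence, which the article states without qualification.

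*Admitted patients need not be non-responders.* Correct. A reader might infer that the rule removes the clearest non-responders. The documents do not support that: admission is not part of the response definition, and the sentence is not limited to admissions for mental-health reasons.

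*Response among patients who remain in outpatient CBT is a legitimate question.* It is, and inpatient care is a co-intervention that affects a later BSI-GSI. But the objective is not worded in that narrower way, and membership of that group is unknown at T0.

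*Counting every admission as non-response would depart from the PREACT outcome definition, which is kept for comparability across subprojects.* This stands. It is the reason for using the observed BSI-GSI wherever it exists and for reporting the analysis without these patients alongside.

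**Conclusion.** The rule is a fault of design. It conditions the prediction cohort on an event that occurs after the predictors are measured and is plausibly related to the outcome. Performance estimated under it applies to patients who turn out not to need inpatient treatment, a group that cannot be recognised when the model would be used.

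The size cannot be derived from the documents. On the assumed ranges (2–10% excluded, all non-responders, true rate 40–60%), about 3–25% of non-responders would be lost and the observed non-response rate would be about 1–7 points too low. Both effects shrink if some of the excluded would have responded.

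A reader might also infer that the reported accuracy will be inflated. The calculation does not support that, because the bias can go in either direction. What holds either way is that the estimate does not describe everyone who provides T0 data and starts treatment.

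**What to change.** For the analysis set only, and settled before the hold-out is evaluated:

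- Do not remove these patients from the prediction analysis. Keep their T0 features and their data up to admission.
- Use the BSI-GSI outcome at T20 and TPost wherever it is available.
- Where it is missing because of a mental-health admission, classify the patient as a non-responder.
- Report the number of patients affected, by reason for admission.
- Present results with and without these patients, so that the version excluding them stays comparable with the PREACT definition.
- If they stay out of the main analysis, limit the conclusion to patients who remain in outpatient CBT.

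The cost is small in data terms, since T0 features precede any admission during therapy. It does need a wording change, a coding rule and a record of the reason for admission. Because the criterion and the outcome definition come from the parent study, agreement within the research unit is also needed. The downside is that non-response then partly includes admission and a co-intervention; the paired analysis shows how much this matters. Clinical decisions about inpatient care are not affected.
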